# **Does iExaminer teaching method improve fundus examination skills?**

## **A randomized controlled trial**

### **1. Background**

All generalist physicians are required to be proficient in fundus examination for detecting prevalent diseases such as diabetic retinopathy, hypertensive retinopathy, papilledema, and retinal hemorrhage. However, it is difficult to provide training in the necessary clinical skills for the fundus examination using the traditional teaching method because there is no way to verify if the student has obtained a proper view of the fundus.

We assumed that sharing of visual field between medical students and the teacher would facilitate the acquisition of those skills. We introduced the iExaminer system to our fundus examination teaching method. The iExaminer system consists of three core components: PanOptic ophthalmoscope, iExaminer adapter, and iExaminer application. This system allows medical students and their teacher to share the same visual perspective.

### **2. Study objectives**

The objective of our research is to investigate whether the iExaminer teaching method (using the iExaminer system) is superior to the traditional teaching method (not using the iExaminer system) for training in fundus examination.

### **3. Selection of study subjects**

#### **a. Selection criteria**

This study's participants will consist of 115 medical students in a general medicine clinical clerkship rotation from September 2017 to July 2018. All data will be collected from those who have consented to the study. This program can be taken by all eligible students and can be taken with or without research consent.

#### **b. Exclusion criteria**

Those who have not given consent to participate in this study are excluded from the subjects.

### **4. Method**

#### **Procedures**

This study was approved by the Ethics Committee of Chiba University School of Medicine (Chiba, Japan). A detailed explanation of the study will be given to all participants, who confirm that they fully understood the information before voluntarily giving informed consent to participate.

#### **Study Design, Setting, and Participants**

A randomized controlled trial is designed to compare the effect of the iExaminer teaching method with the traditional method for teaching the fundus examination. This study's participants will consist of 115 medical students in a general medicine clinical clerkship rotation from 2017 to 2018. The participants will be randomly assigned to either the teaching method group using the iExaminer system (intervention group) or the teaching method not using the iExaminer system (control group). As guidance, faculty advise students about their grip, posture, procedure, angle, and light intensity in each group. For the iExaminer teaching method, faculty teach fundus examination skills using the iExaminer system while sharing screens with students. On the other hand, in the traditional teaching method, faculty teach fundus examination skills while students describe what they are seeing. All instruction time will be standardized to 30 minutes. Three different teachers will be randomly assigned to each session. We create the instructional design and train the faculty to minimize the educational effects.

The participants examine the fundus on the retina simulator (EYE Examination Simulator®; Kyoto Kagaku Co, Kyoto, Japan) using PanOptic ophthalmoscope before and after the educational session (pre-test and post-test). All participants will have watched instructional videos on standard use of the PanOptic ophthalmoscope and will have been prepared for the interpretation of typical fundus findings before the pre-test. In the pre-test and post-test, the students will be assigned three cases using a retina simulator. They will observe one eye for 90 seconds in each case. For each case, they will respond to a multiple-choice question asking if the case was a normal fundus, optic disc edema, pathological optic disc cupping, or not observed. The diagnostic accuracy of funduscopy findings and time taken to identify funduscopy findings will be assessed in pre-test and post-test.

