### **Statistical Analysis**

Statistical analyses will be performed using SPSS Statistics for Windows 22.0 (IBM Corp. Armonk, NY), with the level of significance set at  $P < 0.05$ . Diagnostic accuracy in funduscopy findings and time taken to identify funduscopy findings will be compared between the groups by using the two-way analysis of variance (ANOVA). Assuming an  $\alpha$  error of 0.05,  $\beta$  error of 0.2, power of detection of 0.8, and effect size  $f$  of 0.25, a sample size of 128 tests (a total of 180 tests would be done in each group) will be required for each group to allow for comparison of the diagnostic accuracy of fundus examination.

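### Read as group by pre/post on single tests, the two-way ANOVA leaves case and student in the error, so the group-by-occasion test loses power if the cases differ in difficulty

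*Protocol*

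**What the plan says.** Under Study Design, Setting, and Participants, the protocol randomises students ("The participants will be randomly assigned to either the teaching method group using the iExaminer system (intervention group") and plans for 115 of them. On cases it says: "In the pre-test and post-test, the students will be assigned three cases using a retina simulator". The possible answers are a normal fundus, disc edema, pathological cupping, or not observed. Accuracy and time are both assessed at pre-test and post-test.

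Under Statistical Analysis, both outcomes "will be compared between the groups by using the two-way analysis of variance (ANOVA". Neither factor is named, and no student or case term is mentioned. The sample is counted in tests, not students: "a sample size of 128 tests (a total of 180 tests would be done in each group) will be required for each group".

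**The concern.** A two-way ANOVA has two factors. The comparison is between groups, so group is one. The outcomes are measured before and after teaching, so occasion is the natural second. Case then falls into the residual, as does the student. If case were the second factor, occasion would drop out, so two factors cannot hold all three.

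If both groups see the same cases, a hard case lowers both groups alike. It adds nothing to the true uncertainty of the group comparison, but the ANOVA still charges it to the error. In a pre/post teaching trial the natural measure of the teaching effect is the group-by-occasion interaction. For that term, a residual inflated by case makes the test conservative, and a real benefit is more likely to be missed. If case sets differed between students, chance differences in case mix would also enter the contrast.

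**Working it through.** **The plan's own figure.** With f = 0.25, alpha 0.05 and a 1-df effect, the noncentrality is f²N = 0.0625 × 128 = 8, which gives power 0.801. So 128 reproduces as the total, not as the number for each group. 256 tests give 0.979 and 360 (180 per group) give 0.997. This is a separate matter from the present point.

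**Inputs.** From the protocol: 115 students (58 + 57) and three cases per occasion, hence 115 × 6 = 690 tests. Assumed, because the protocol gives neither: case difficulty and within-student correlation.

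- Correct rates 30/50/70%: case variance (0.04 + 0 + 0.04)/3 = 0.0267, over 0.25 = 10.7% of the variance.
- Correct rates 20/50/80%: (0.09 + 0 + 0.09)/3 = 0.06, over 0.25 = 24%.

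**Formulas.** Let the shares of student, case and residual variance be s, c and e, with s + c + e = 1. A test-level ANOVA with neither term uses 1 as the variance of a test. The ratio of its standard error to the true one is:

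- interaction, stable student differences: 1/√e
- interaction, with a part u of s varying by student and occasion: 1/√(e + 3u)
- post-test contrast: 1/√(e + 3s)
- group main effect over six tests: 1/√(e + 6s)

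Type I error is 2[1 − Φ(1.96 × ratio)]. Example: c = 0.107 and s = 0 give e = 0.893, ratio 1.058, 1.96 × 1.058 = 2.074, type I error 3.8%.

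| Case share | Student share | Interaction, stable students | Interaction, u = s/2 | Post-test contrast | Group main effect |
|---|---|---|---|---|---|
| 10.7% | 0 | 3.8% | 3.8% | 3.8% | 3.8% |
| 10.7% | 0.1 | 2.8% | 4.4% | 6.1% | 9.7% |
| 10.7% | 0.2 | 1.9% | 4.9% | 8.5% | 15.4% |
| 10.7% | 0.3 | 1.1% | 5.5% | 10.9% | 20.5% |
| 24% | 0 | 2.5% | 2.5% | 2.5% | 2.5% |
| 24% | 0.1 | 1.6% | 2.9% | 4.5% | 8.1% |
| 24% | 0.2 | 0.9% | 3.5% | 6.9% | 14.0% |
| 24% | 0.3 | 0.4% | 4.0% | 9.3% | 19.2% |

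At a case share of 3% with independent answers, the ratio is 1/√0.97 = 1.015 and type I error 4.7%, which is immaterial.

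Simulations of 0/1 answers with no student correlation gave 3.4-3.9% for the interaction at shares of about 11-15%, and 2.1-3.0% at 24-29%. With case in the model the rate was about 5%.

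**Power for an assumed 15-point extra gain, no student correlation.** The critical value is 1.96 × the ANOVA standard error; power is Φ((0.15 − critical value)/true standard error). Tests per occasion are 57 × 3 = 171 and 58 × 3 = 174.

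- Pre-test 60/40/20%, control post-test 82/70/40%, intervention 97/85/55%. Average error variance over the four cells is 0.2191 without case and 0.1901 with it (case share 13%). ANOVA standard error without case: √(0.2191 × (2/171 + 2/174)) = 0.0713; with case 0.0664; true 0.0664. Power is 56% without case and 62% with it.
- Pre-test 80/40/15%, control post-test 82/60/35%, intervention 97/75/50%. Error variance 0.2323 and 0.1781 (share 23%). Standard errors 0.0734 and 0.0643; true 0.0643. Power is 54% and 65%.

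Simulations with the same or similar rates gave 52-54% rising to 57-61%, and 52-53% rising to 63-66%.

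**Adding case alone.** For the post-test contrast the ratio becomes √((s + e)/(e + 3s)). At 10.7% case share, type I error rises from 6.1% to 7.7% (s = 0.1), 8.5% to 10.3% (0.2) and 10.9% to 13.0% (0.3).

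**The case against.** **The factors are not named, and a fuller model may stand in an analysis plan that is not shown.** This stands in part. The absence of a case term is an inference, not a statement in the protocol. What the protocol does fix is a two-factor ANOVA with tests as the counted unit, and that cannot hold group, occasion and case. A repeated-measures version on student scores would escape the problem, but counting in tests points away from it.

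**On the protocol's own inputs power is 0.997, so nothing is lost.** True for a 1-df effect of f = 0.25 on 360 tests. In a two-by-two layout, however, an interaction of f = 0.25 is a difference of differences of 4 × 0.25 = 1 within-cell SD. With SD √0.2191 = 0.468, that is 47 percentage points. A 15-point gain is f = 0.15/(4 × 0.468) = 0.08. The loss is immaterial for a very large effect and material for a moderate one. The 15 points are an assumption.

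**The student, not the case, is the larger defect.** This stands. A reader might infer that all the error bars are too wide, or that student correlation always pulls the opposite way from case. Neither is supported. For the post-test contrast the bars are too wide only if case variance exceeds twice the student variance (c > 2s); otherwise they are too narrow. The group main effect is more exposed still. For the interaction, stable student differences act in the same direction as case, and at moderate correlation they add more to the excess: at 10.7% case share the ratio goes from 1.06 to 1.20 when s = 0.2.

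**A complete per-student score removes the case problem.** This also stands, and it is one of the two remedies.

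**Conclusion.** The point holds for the group-by-occasion test, on the reading that the two factors are group and pre/post and that both groups see the same cases. With case shares of 11-24% and no student correlation, type I error is about 2.5-3.9% and about 5 to 12 points of power are lost for a 15-point gain. With nearly equal cases the effect is negligible. Stable student differences make this test more conservative. If students also differ in how much they change, the conservatism shrinks and can vanish (5.5% at 10.7% case share, s = 0.3, half of it student-by-occasion).

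It does not hold as a general statement that the intervals are too wide: at 11% case share the post-test contrast runs at about 6-11% for student shares of 0.1-0.3. Case difficulty, student correlation and the size of the gain are all assumptions. The same algebra applies to time, but the protocol offers nothing from which to size it.

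**What to change.** Name the model terms. Analyse accuracy and time with group, occasion and their interaction, with case and case-by-occasion as fixed factors, together with student and student-by-occasion terms. For accuracy, use a logistic model clustered by student. Alternatively, when every student has all three cases, analyse one score per student at each occasion; the case effect then cancels. State that both groups receive the same case set at each occasion.

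Case should not be added without the student terms, because that makes the post-test comparison more anti-conservative.

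The cost is 2 degrees of freedom for case and 2 more for case-by-occasion, out of 690 tests, and no new data. If per-student scores are complete, modelling case adds little; the gain is then mainly for time and for incomplete case sets.

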### **Statistical Analysis**

Statistical analyses will be performed using SPSS Statistics for Windows 22.0 (IBM Corp. Armonk, NY), with the level of significance set at  $P < 0.05$ . Diagnostic accuracy in funduscopy findings and time taken to identify funduscopy findings will be compared between the groups by using the two-way analysis of variance (ANOVA). Assuming an  $\alpha$  error of 0.05,  $\beta$  error of 0.2, power of detection of 0.8, and effect size  $f$  of 0.25, a sample size of 128 tests (a total of 180 tests would be done in each group) will be required for each group to allow for comparison of the diagnostic accuracy of fundus examination.

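### The groups are compared by an unspecified two-way ANOVA that does not adjust for the pre-test every student takes; post-test accuracy adjusted for pre-test would be the clearer and more powerful primary contrast

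*Protocol*

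**What the plan says.** Under Study Design, Setting, and Participants, students are randomised to the two teaching methods and tested before and after the session: "In the pre-test and post-test, the students will be assigned three cases using a retina simulator". Both outcomes are recorded on both occasions: "The diagnostic accuracy of funduscopy findings and time taken to identify funduscopy findings will be assessed in pre-test and post-test".

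Under Statistical Analysis, the protocol states: "Diagnostic accuracy in funduscopy findings and time taken to identify funduscopy findings will be compared between the groups". The same sentence gives the method: the outcomes "will be compared between the groups by using the two-way analysis of variance (ANOVA"). The factors are not listed, the tested term is not identified, and neither a repeated-measures structure nor a baseline covariate is mentioned. The sample-size statement takes an effect size f "of 0.25, a sample size of 128 tests (a total of 180 tests would be done in each group"), which "will be required for each group to allow for comparison of the diagnostic accuracy of fundus examination".

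**The concern.** The question is whether students taught with the iExaminer system perform better after teaching. Teaching cannot have affected the pre-test, and randomisation makes its expected value equal in the two groups. The pre-test is therefore most useful as a covariate for the post-test. A two-way ANOVA on group and occasion uses it differently, as a second outcome occasion.

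That matters in two ways. If the comparison of groups is read as the group main effect, the reported difference is diluted by an occasion on which no effect is possible. If it is read as the interaction, the difference is correct but carries the full noise of a three-case pre-test. In both cases the trial is more likely to miss a real benefit than it need be with the same data. Leaving the term open also allows it to be chosen after the results are seen.

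**Working it through.** **Inputs from the protocol.** Significance level 0.05, power 0.8, f = 0.25, 128 tests required and 180 planned per group, 115 students, three cases per student on each occasion. The allocation ratio is not stated; 1:1 is assumed, so 115/2 = 57.5 students per group. The pre/post correlation rho is not given, so a range is shown.

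**The plan's own figure.** For f = 0.25 and one numerator degree of freedom, the noncentral F with lambda = N × f² reaches 80.1% power at N = 128 in total, or 64 per group. The figure of 128 is reproduced as a total, not as a number for each group. That is a separate matter. What counts here is that f = 0.25 for a two-group comparison on one occasion is a difference of 2 × 0.25 = 0.5 SD.

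**What each term estimates.** Let the expected means be 0 at both pre-tests, 0 at the control post-test and D at the intervention post-test.
- Group main effect: (0 + D)/2 − (0 + 0)/2 = D/2.
- Group by occasion: (D − 0) − (0 − 0) = D.
- Post-test adjusted for pre-test: D.

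**Variance of each, at student level with SD 1 on each occasion.**
- Mean of pre and post: (1 + rho)/2.
- Raw change: 2(1 − rho).
- Adjusted post-test: 1 − rho².

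The ratio of raw change to adjusted post-test is 2(1 − rho)/[(1 − rho)(1 + rho)] = 2/(1 + rho), that is 1.67, 1.33 and 1.18 at rho 0.2, 0.5 and 0.7.

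**Power for D = 0.5 SD, continuous outcome.** Power = Φ(δ/[s√(2/n)] − 1.96), with n = 57.5, δ the quantity estimated and s the square root of the variance above. Worked at rho = 0.5, where √(2/57.5) = 0.1865:
- Main effect: 0.25/(0.866 × 0.1865) = 1.548; Φ(−0.412) = 34%.
- Raw change: 0.5/(1 × 0.1865) = 2.681; Φ(0.721) = 76.5%.
- Adjusted post-test: 0.5/(0.866 × 0.1865) = 3.096; Φ(1.136) = 87%.

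| rho | Main effect: power (n per group for 80%) | Raw change | Adjusted post-test |
|---|---|---|---|
| 0.2 | 41% (151) | 56% (101) | 78% (61) |
| 0.5 | 34% (189) | 77% (63) | 87% (48) |
| 0.7 | 31% (214) | 93% (38) | 96% (33) |

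A post-test comparison that ignores the pre-test has 76.5% power whatever rho is. Below rho = 0.5, raw change is therefore worse than not using the pre-test at all. Simulation with 57 students per group gave mean estimates of 0.25 for the main effect, and 0.49 to 0.50 for both raw change and the adjusted post-test, against a true 0.50.

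**Power for a three-case accuracy score.** The accuracies are assumptions, not protocol values: 45% before teaching in both groups, 55% versus 70% after; 57 and 58 students; three binary cases per occasion; latent intraclass correlation 0 to 0.4. All three analyses use one value per student, so that clustering of cases is not mixed up with baseline adjustment.

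| Analysis | Mean estimate | Power |
|---|---|---|
| Group main effect | 7.5 points | about 25-52% |
| Raw change | 15 points | about 54-64% |
| Post-test adjusted for pre-test | 15 points | about 76-83% |

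**The case against.** The strongest objection is that the protocol never says the factors are group and occasion. The design also has three teachers and three cases per test, and either could be the second factor in an ANOVA of post-test results. Nothing would then be averaged with the pre-test. This stands: the halving and the power losses are conditional on a group-by-occasion model. Measuring both outcomes on both occasions makes that the natural reading, not a certain one.

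A reader might infer that the plan will report half the true effect. The text does not support that. Halving belongs to the main effect alone, the interaction recovers the full difference, and a general phrase about comparing groups can cover either term.

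A reader might also infer that f = 0.25 commits the trial to detecting a full SD, or about 50 percentage points for a binary result with SD 0.5. In a 2 × 2 layout of group by occasion, both the group and the interaction deviations are ±D/4. So f = D/(4 SD), and f = 0.25 would need D = 1 SD. But the protocol's 180 tests per group is 60 × 3, one occasion. With 115 students, one occasion gives 57.5 × 3 = 172.5 tests per group and both give 345. The effect size thus appears to be set on a single occasion, where it means 0.5 SD.

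If every test is treated as an independent observation, the main effect appears to have about 50% power even with correlated cases. At an intraclass correlation of 0.25 that analysis has a type I error of about 14%, so it is not a fair comparator.

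Finally, factors and covariates are often settled in a SAP, which is not at hand, and under randomisation raw change is unbiased. What remains is that the protocol does commit to a method, that this method as written leaves the baseline unadjusted, and that the adjusted post-test has the highest power at every rho tabulated. Its margin over raw change is small when rho is high (96% versus 93% at 0.7).

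**Conclusion.** The point holds as a recommended improvement, not as a proven error in every reading. The protocol fixes a two-way ANOVA without naming its terms and without using as a covariate a pre-test that it collects from every student.

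If the factors are group and occasion, the main effect estimates half the post-teaching difference. The interaction estimates all of it, at 1.18 to 1.67 times the variance of the adjusted comparison for rho from 0.7 down to 0.2. In the assumed 15-point scenario, the gain is from about 25-52% power (main effect) or 54-64% (raw change) to 76-83%.

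These sizes rest on 1:1 allocation, equal expected pre-test means, one summary value per student, and assumed accuracies and correlations. The direction does not depend on the assumed rates. The size of the gain over raw change does depend on rho.

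**What to change.** Make the primary analysis the between-group difference in each student's post-test accuracy, adjusted for that student's pre-test accuracy. Use ANCOVA on the student score, or a logistic model of the post-test results with pre-test accuracy as covariate and clustering by student. Report the adjusted difference with a 95% CI. State that the f = 0.25 in the sample-size calculation refers to this single-occasion contrast. Analyse time to identify findings in the same way, with post-test time adjusted for pre-test time.

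If a group-by-occasion ANOVA is kept as a secondary analysis, name its factors and state that the interaction, not the group main effect, tests the teaching method.

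The cost is wording in the protocol or SAP, settled before the results are seen. No extra data are needed, since the pre-test is already planned for everyone.

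### Accuracy and time are each tested at P < 0.05 and neither is named primary, so the protocol leaves open which one decides superiority

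*Protocol*

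**What the plan says.** The Study objectives section of the protocol asks one question: whether the iExaminer method "is superior to the traditional teaching method (not using the iExaminer system) for training in fundus examination". It does not say on which measure.

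The section on study design, setting and participants gives two measures side by side, without rank: "The diagnostic accuracy of funduscopy findings and time taken to identify funduscopy findings will be assessed in pre-test and post-test".

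The Statistical Analysis section applies one significance level, P < 0.05, to all analyses and treats the two measures alike: "Diagnostic accuracy in funduscopy findings and time taken to identify funduscopy findings will be compared between the groups by using" a two-way ANOVA.

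The only sign of a ranking comes in the sample-size sentence of the same section, where the number of tests is chosen "to allow for comparison of the diagnostic accuracy of fundus examination". Time is not mentioned there.

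The protocol does not use the terms primary or secondary for any outcome. It sets no order of testing, does not require success on both outcomes, and does not divide the 0.05 between them.

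**The concern.** One objective is served by two outcomes of equal standing, each tested at the full 0.05. If either may carry the conclusion, the error rate of the overall claim is higher than that of one test.

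There is a second problem that does not depend on the error rate. Students have 90 seconds per case and answer a multiple-choice question, so a student can be quick and wrong. If one teaching method gives faster but less accurate examinations, the protocol does not say whether superiority has been shown. That choice would then be made after the results are known.

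**Working it through.** **Inputs from the protocol (Statistical Analysis section)**
- Significance level 0.05, the same for both outcomes.
- Two outcomes compared between groups: diagnostic accuracy and time taken.
- Sample size for accuracy only: alpha 0.05, power 0.8, effect size f = 0.25, stated result 128 tests for each group.

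**Input not in the protocol**
- The correlation between the two test statistics. I assume an absolute value from 0 to 0.9.

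**The plan's own figure.** For an ANOVA F test with 1 numerator degree of freedom, the noncentrality is N × f² = 128 × 0.0625 = 8. This gives power 0.801 at a *total* N of 128. So 128 reproduces as the total for both groups, not as the number for each group. That labelling is a separate matter and does not affect this point. What matters here is that the calculation spends the whole 0.05 on accuracy.

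**Two-sided risk, either outcome counting**
- Independent: 1 − (1 − 0.05)² = 1 − 0.9025 = 0.0975.
- Ceiling under any dependence: 0.05 + 0.05 = 0.10.
- Correlated: 1 − P(|Z₁| < 1.96 and |Z₂| < 1.96), with Z₁ and Z₂ bivariate normal. By symmetry this depends only on the absolute correlation.

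| Absolute correlation | Risk of at least one false rejection |
|---|---|
| 0 | 0.0975 |
| 0.3 | 0.0951 |
| 0.5 | 0.0907 |
| 0.7 | 0.0835 |
| 0.9 | 0.0704 |

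One test alone: 0.05.

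**Risk of a false claim in favour of iExaminer.** Orient both statistics so that positive values favour iExaminer (more accurate, faster).
- One test: 0.05 / 2 = 0.025.
- Either of two, independent: 1 − 0.975² = 0.0494.
- Correlation 0.5: 0.0454. Correlation 0.9: 0.0352.
- Ceiling, including negative correlation: 0.025 + 0.025 = 0.05.

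**With one outcome named primary.** The two-sided error of the superiority claim is 0.05, and the total N at f = 0.25 stays at 128.

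**With two co-equal outcomes at 0.025 each.** The error is 1 − 0.975² = 0.0494 if independent and at most 0.05. The total N for 80% power at f = 0.25 rises from 128 to 155 tests.

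**The case against.** **The sample size already points to accuracy.** This is true, and it shows what the sponsor probably intends. It remains a hint: nothing limits the superiority claim to accuracy, and time is compared at the same level in the same sentence.

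**A statistical analysis plan may settle it.** Multiplicity procedures and the choice of ANOVA term can reasonably be left to that document, and I raise neither as a gap. Naming the outcome that answers the objective is different. It defines the trial's question and belongs in the protocol.

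**The protocol does not state an either-or rule.** This stands. A reader might infer that one significant result is declared sufficient, but no sentence says so. The protocol is silent, and its silence permits that use. If both outcomes had to succeed, there would be no inflation. The error rates above therefore apply only if either outcome may count.

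**The objective is directional.** This also stands. A reader might take 9.75% as the chance of wrongly declaring iExaminer superior. Half of each test's false rejections would favour the traditional method, so the relevant figure is at most about 5% against 2.5%.

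**The outcomes are unlikely to be independent.** Both come from the same observation of the same case. Correlation of either sign lowers the two-sided rate, so 9.75% is the upper end of the range shown.

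**A larger count of tests is tempting.** A reader might assume that each ANOVA gives a group term and a group-by-occasion term, count four tests and compute 1 − 0.95⁴ = 18.5%. The protocol does not support this. It never names the two factors, it does not make every term a basis for the claim, and four independent tests would be needed.

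**Conclusion.** The point holds. The protocol has one superiority objective and two unranked outcomes, each tested at the full 0.05, with no rule for disagreement between them.

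If either may count, the risk of a false claim favouring iExaminer is up to about double that of a single test: at most about 5% instead of 2.5%. In two-sided terms it is about 7% to 9.75% instead of 5%. The range rests on an assumed absolute correlation of 0.9 to 0 and on approximately normal test statistics.

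The rates also assume that each test holds its nominal level. The protocol counts tests rather than students, and each student contributes several, so the true rates could be higher. The lack of a rule for conflicting outcomes remains whatever the correlation.

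This should be corrected. It does not invalidate the design.

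**What to change.** In the Statistical Analysis section:

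1. Name diagnostic accuracy as the sole primary outcome, tested at 0.05. It is the outcome on which the sample size already rests.
2. Name time to identification as secondary, with a confirmatory test only if accuracy is significant.
3. State that the superiority conclusion is based on accuracy.

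The sample-size sentence speaks of diagnostic accuracy without specifying the test occasion. Naming accuracy as primary therefore agrees with it, but it gives no support for choosing post-test accuracy in particular. How the pre-test enters the analysis can be settled in the statistical analysis plan.

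The cost is a few sentences and no change in the calculated sample size. The loss is that time alone can no longer support the superiority claim. If the sponsor wants to keep that option, 0.025 for each outcome also controls the error, at the price of the larger sample shown above.

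### The sample size is counted in tests and the two-way ANOVA has no student term, although students are randomised and each supplies three tests before and three after teaching

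*Protocol*

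**What the plan says.** Protocol, section 4, Study Design, Setting, and Participants, makes the student the randomised unit: "The participants will be randomly assigned to either the teaching method group using the iExaminer system (intervention group") or the control group. On numbers: "This study's participants will consist of 115 medical students in a general medicine clinical clerkship rotation from 2017 to 2018". On testing: "In the pre-test and post-test, the students will be assigned three cases using a retina simulator". Each student therefore gives 3 results on each of 2 occasions, 6 in all.

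Protocol, section 4, Statistical Analysis, says that both outcomes, accuracy and time, will be "compared between the groups by using the two-way analysis of variance (ANOVA"). It does not name the two factors or the rows of the analysis. It mentions no student effect, repeated-measures structure, ICC or design effect. The sample size, given for accuracy, is stated only in tests: "a sample size of 128 tests (a total of 180 tests would be done in each group) will be required for each group".

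**The concern.** Results from one student share that student's skill, so they are likely to be positively correlated. An ordinary two-way ANOVA on tests treats them as independent. With 115 students it would have 115 × 6 = 690 rows but only 115 randomised units, and its error term would not reflect the variation between students that the group comparison has to be judged against.

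The trial's stated aim is to show that the iExaminer method is superior. If the standard error of the group comparison is too small, a claim of superiority can arise by chance more often than the 5% the protocol promises. The sample-size statement has the same flaw: it uses a formula for independent observations and counts one student's three readings as three sample units.

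**Working it through.** **Inputs from the protocol.** Significance level 0.05, power 0.80, f = 0.25, 128 tests required and 180 planned per group, 115 students, 3 tests per occasion, 2 occasions.

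**Assumptions.** Allocation 1:1, so 115/2 = 57.5 students per group. The ICC is not in the protocol; 0.1, 0.3 and 0.5 are the working range. f = 0.25 is taken to apply to a single test; for two groups it equals a standardised difference d = 0.5.

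**1. The protocol's own figure.** Noncentral F power for a 1-df effect with independent observations and noncentrality N × f²:
- N = 128 in total (64 per group) gives power 0.801.
- N = 256 (128 per group) gives power 0.979.

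So 128 reproduces as a total and not for each group. Effects with 2, 3 and 5 df need totals of 158, 179 and 211; none gives 128 per group.

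**2. The unit being counted.** 180/3 = 60 students per group at three tests each, close to 57.5 × 3 = 172.5. Six tests per student would give 57.5 × 6 = 345. The planned 180 therefore looks like about 60 students times three tests on one occasion, each test counted as one sample unit.

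**3. False-positive rate if tests are analysed as independent.** Actual level = 2 × (1 − Φ(1.96/√V)), where V is the ratio of true to assumed variance:
- post-test comparison, three tests per student: V = 1 + 2 × ICC
- group main effect over all six tests, equal correlation: V = 1 + 5 × ICC

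| ICC | V, post-test | Level | V, six tests | Level |
|---|---|---|---|---|
| 0.1 | 1.2 | 7.4% | 1.5 | 11.0% |
| 0.3 | 1.6 | 12.1% | 2.5 | 21.5% |
| 0.5 | 2.0 | 16.6% | 3.5 | 29.5% |

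Null simulations with binary results, 4,000 trials per setting and a random student intercept, agree: the group main effect was rejected in about 10%, 16%, 19% and 23% of trials at ICC 0.09, 0.17, 0.25 and 0.33. A student-level analysis of the post-test adjusted for the pre-test held 4.4% to 4.8% in the same data.

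**4. Group-by-time.** With correlation r_w between tests on the same occasion and r_b across occasions, V = 1 + 2r_w − 3r_b.
- Equal correlation: V = 1 − ICC. At ICC 0.1, 0.3 and 0.5 the level is 3.9%, 1.9% and 0.6%, which is conservative.
- r_w = 0.3, r_b = 0.1: V = 1.3, level about 8.6%.
- r_w = 0.4, r_b = 0.2: V = 1.2, level about 7.4%.

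Simulations with extra same-occasion correlation gave 7% to 11%.

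**5. Power with clustering respected.** Divide the tests per group by 1 + 2 × ICC and take d = 0.5:

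| Tests per group | ICC 0.1 | 0.3 | 0.5 | 1 |
|---|---|---|---|---|
| 64 | 0.73 | 0.61 | 0.52 | 0.37 |
| 128 | 0.96 | 0.89 | 0.81 | 0.64 |
| 172.5 (115 students) | 0.99 | 0.96 | 0.91 | 0.77 |
| 180 | 0.99 | 0.96 | 0.92 | 0.78 |

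By the normal approximation, 80% power needs 63 independent observations per group. The largest tolerable design effect is 180/63 = 2.86 (ICC about 0.93) for 180 tests and 172.5/63 = 2.74 (ICC about 0.87) for 115 students.

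**The case against.** The strongest reply is that the protocol never says that the ANOVA runs on tests. A group-by-time ANOVA with repeated measures on student scores is often loosely called two-way, fits the pre/post design, and would keep the error rate near nominal. A statistical analysis plan that is not shown could specify it. This stands in part: the test-level analysis is inferred, so the claim about P-values has to be conditional. The inference is the natural one, though, because the requirement is given in tests and tied to the comparison of accuracy. A student-level analysis would cure the P-values but would no longer match a sample size counted in tests, so the section needs correcting either way.

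Four stronger readings are tempting, and the document does not support them:

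- **The trial is underpowered.** Clustering does cost power. But 128 is really the total, so the planned numbers keep about 80% power up to an ICC near 0.9 if f = 0.25 applies per test. If f were meant for a student's score, 57.5 students per group would give about 0.77 before any gain from the pre-test; the protocol ties f to a count of tests, so this is not established.
- **The group-by-time test is conservative.** This holds only if all six tests correlate equally.
- **The main-effect error of 11% to 29% is what the trial faces.** That contrast averages in the pre-test, where teaching can have no effect. The post-test or group-by-time contrast is the more natural one, and the protocol does not say which decides.
- **ANOVA is invalid because accuracy is binary.** The coding is not stated, and the adjusted student-level analysis of simulated binary data held its level. This point is secondary.

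**Conclusion.** The point holds. The unit in which the sample size is stated is not the randomised unit, and the analysis as described does nothing about correlation within students.

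If the ANOVA is run on tests, the nominal 5% becomes about 7% to 17% for a post-test comparison and about 11% to 29% for the group main effect, over an assumed ICC of 0.1 to 0.5. The group-by-time error has no known direction. These sizes rest on the assumed ICC and, for the main effect, on equal correlation among the six tests.

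The power statement is wrong on two counts: 128 is a total presented as a per-group number, and no design effect is applied. Neither shows that the trial has too few students.

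**What to change.** - **Analysis.** Make the student the unit for both outcomes. Either use one row per student, with the post-test score (0 to 3 correct) or mean time adjusted for the pre-test value, or model the individual tests with a mixed model or GEE clustered by student. Name the factors and the contrast that answers the superiority question.
- **Sample size.** Restate it in students, about 57 or 58 per group, with the design effect 1 + 2 × ICC shown over a stated ICC range. Say whether f = 0.25 refers to a single test or to a student's score.
- **Figure.** Correct the 128: at f = 0.25 with 1 df it is the total of independent observations for 80% power, or 64 per group.

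The cost is wording and analysis code. No extra students, tests or data are needed, and the SPSS version that the protocol names already provides GEE and generalised linear mixed models.
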